##### Quantitative data collection and analysis

Informed consent and data collection procedures will be completed anonymously via Lime Survey at the participant’s convenience during a 4-week study window. Survey items will be informed by the coding categories and constructs identified in the qualitative strand of phase 1 (described above), as well as include validated measures from health professions education, implementation science, and family violence literature. Specifically, items will ask participants to self-report on their (a) socio-demographic characteristics and previous training in family violence; (b) readiness to undertake family violence training (e.g., Brief Readings to Change Scale [71]); (c) attitudes toward incorporating research evidence into their practice (e.g., Evidence Based Practice Attitudes Scale); (d) preparedness to address family violence in practice (e.g., an adapted Physician Readiness to Manage Intimate Partner Violence Survey (PREMIS) [72, 73] and Healthcare Provider Attitudes toward Child Maltreatment Reporting Scale [74, 75]); and (e) preferences, barriers, and facilitators related to participating in education activities focused on family violence (e.g., online vs. face-to-face learning, etc.) [76]. Participants who complete the anonymous survey will be given the option to enter their name in a draw to win one of six $500.00 honorariums.

All data from our Lime Survey platform will be exported into our data analysis software, SPSS (version 28). Estimates of the variability and saliency of HSSP learning and implementation needs, and preferences will be generated via statistics of dispersion and central tendency. Differences across provider groups and specialities will be evaluated using single-level correlation and regression analysis.

### Phase 2: VEGA usability and exploratory assessment of education outcomes

According to the AIFs, stage 3 (initial implementation) refers to the point at which changes begin to occur within the overall practice environment. For the purposes of this project, this would include not only changes in HSSP KASB, but also changes in overall health and social service sector capacity to be able to safely recognize and respond to family violence. Guidelines from the developers of the AIF indicate that stage 3 is the point at which implementation challenges present themselves, as do opportunities to refine and expand the suite of strategies to support successful implementation and realize intervention impact [36]. Given the probability of implementation failure to occur at this stage, data-driven, pilot-based approaches are encouraged [77, 78]. For this reason, we will pilot VEGA through the application of usability testing. Usability testing focuses on the evaluation of intervention technology and is an essential step for realizing e-learning impacts; this is especially the case in health professions education [79–82].

Usability testing follows a data transformation variant of an embedded mixed method research design to generate a description of (a) intervention usability (i.e., the extent to which VEGA can be used by HSSP users to achieve their learning goals with effectiveness, efficiency, and satisfaction) and (b) educational impact [83]. Using this design, quantitative and qualitative strands of data collection are collected from the same participants during one data collection visit.

#### The intervention: Violence, Evidence, Guidance, Action (VEGA) project

VEGA is an online educational intervention that was created for Canadian HSSPs to develop and improve their KASB related to recognizing and responding to all forms of family violence. The intervention was developed using an iterative design process that incorporated systematic evidence reviews of the family violence literature, environmental scans of existing and relevant training resources, and consultation with clinical and research experts in the areas of family violence, instructional design, and health professions education. An important element of VEGA’s development also included repeat consultation from clinicians and scientists belonging to 22 national-level HSSP organizations in Canada.

VEGA follows a participatory, encounter-based curriculum over the course of four core learning modules; learning module content and pedagogical approaches are informed by evidence-based models of adult learning and cognitive processing [84–88] and follow the VEGA Competency Framework for Recognizing & Responding Safely to Family Violence. VEGA can be completed as a self-directed educational activity or it can be delivered by trained facilitators in a virtual or face-to-face workshop. Time to completion is approximately 3 h. Although freely available to HSSPs across Canada, the intervention has yet to undergo formal evaluation to determine its effectiveness. More information about VEGA and its competency framework can be found at vegaproject.mcmaster.ca.

#### Qualitative research strand

##### Sampling and qualitative data collection

Evidence indicates that 95% of usability problems can be identified with usability testing among a purposeful sample of five-to-ten potential end-users. In the case where the intent of the intervention is to meet the learning needs of several different end-users, there is a need to ensure there is sufficient user-testing with each user type [89, 90]. Given this information, we will use purposeful, criterion-based sampling [64, 65] to recruit a convenience sample of up to 20 trainee (~ 10 social work; 10 physician) and 20 licensed practitioners (~10 social work; ~ 10 practitioners) to participate in this phase of the project. Eligible participants will be those who are (a) 18 years of age or older; (b) a trainee or practicing physician or social worker residing in Hamilton, Calgary, or Montreal; and (c) willing to complete user-testing procedures synchronously with a member of the research team.

Enrolled participants will complete the self-directed format of the VEGA intervention using a think-aloud protocol [89]. Specifically, the participant will be prompted by a member of the research team to navigate through the VEGA intervention to complete a series of learning tasks that follow VEGA’s recommended learning pathway while “thinking aloud.” That is, participants will be prompted by the research team member to say their thoughts and activities “out loud” as they move through the intervention (e.g., “I am now scrolling down to see more content;” “I can’t locate the button to move forward in this module”). The think-aloud protocol will be audio-recorded and transcribed verbatim for qualitative data analysis. All participants will be offered continuing medical education credits (physicians; physician trainees) or a certificate of continuing education participation (social workers; social work trainees) for completing the VEGA intervention via the think-aloud protocol.

##### Qualitative data analysis and data transformation

De-identified think-aloud transcripts will be analyzed using framework analysis [91, 92]. This process involves the a priori indexing of the types of usability problems detailed by Hornbaek [93] and Hvannberg and Law [94] into NVivo data management software and completing iterative reviews of the transcripts to apply the indexed usability problems to the transcribed data. Application of usability problems to the data will be completed independently by two members of the research team and will allow for the determination of usability problems (if any), problem types, their frequency, and their severity (1 = mild problem, 2 = moderate problem, 3 = serious problem, 4 = critical problem). Differences in indexing of user problems will be resolved via consensus discussion among the analysts and the leads of the research team.

#### Quantitative research strand

##### Data collection

The quantitative strand of data collection follows a pre-post-research design [95]. Specifically, the sample participants who enroll in the qualitative portion above will self-complete a series of research assessments on our Lime Survey platform at two timepoints: immediately prior (time 1; pre-assessment) and immediately following their think-aloud protocol (time 2; post-assessment). Research assessments will be embedded in a hyperlink that is sent to participants via email 25 min prior to the start of the think-aloud protocol, as well as again immediately after the think-aloud protocol. In addition to socio-demographic characteristics (sex at birth, gender identification, age, location, professional status and discipline, years of practice), quantitative assessments pre- and post-the think-aloud protocol will include the same validated measures of KASB administered in the quantitative strand of phase 1, as well as a vignette-based assessment of knowledge and skill accuracy related to recognizing and responding to family violence. Vignette-based assessment methods are a common, robust measure of practitioner knowledge and skill accuracy related to family violence [30–32], as well as in medical and health professions education, more generally [96–98].

The post-assessment will also ask participants to self-report the extent to which they perceive their current clinical environment to be safe to discuss complex issues related to family violence (e.g., Safety Culture Scale [99, 100]), as well as their satisfaction with usability of the VEGA intervention (e.g., System Usability Scale (SUS)) [101, 102]. Validated measures will be supplemented with data that is compiled and tracked by the project’s research staff; this will include tracking (a) VEGA usability effectiveness via “learning task completion” during the think-aloud protocol with a yes/no checklist, (b) user time on “learning task,” (c) missing data at the item and group level at the pre- and post-assessment timepoints, and (d) the average time needed to complete pre- and post-research assessments. An honorarium ($150.00 for a practicing social worker or physician; $75.00 for resident physicians and trainee social workers) in the form of an e-gift card will be provided as a token of appreciation for the completion of quantitative measures.

##### Quantitative and integrated data analysis

Quantitative data will be analyzed and interpreted via estimates of central tendency and dispersion. Specifically, the proportion of participants reporting “satisfactory” usability for the VEGA intervention (i.e., a score of > 70) will be generated for trainees and practitioners by discipline (social work, medicine) [89, 93, 94]. In addition, the mean and range of SUS scores for the entire sample will be reported, as will the mean and range for participants who reported an SUS adjective rating of (a) poor, (b) “OK,” (c) good, (d) excellent, and (e) best imaginable. We will compute the range of missing data for all quantitative measures, with feasibility of collecting quantitative outcome data indicated by less than 20% missing data at the participant and group level for each timepoint. We will also generate and present (a) correlations between continuous user satisfaction scores and pre/post-practitioner scores on KASB measures and (b) cross-tabulations of satisfaction scores, the rate of usability problems, problem types, and problem severity [33, 103]. Upon review of results, team members will decide which usability changes — if any — need to occur prior to initiating phase 3 of the RISE Project. We will partner with the VEGA team to implement those changes to the intervention.

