Phase 1 (2020–2021)	QUAL ➔ quan	*Qualitative research question:* How do trainee and licensed physicians and social workers residing in the provinces of Ontario, Quebec, and Alberta describe their learning and implementation needs and preferences related to education on family violence? *Quantitative research question:* Among the licensed and trainee physicians and social workers in Canada, what are the most salient learning and implementation needs and preferences related to education on family violence? *Mixed methods research question:* Are the learning and implementation needs and preferences related to education on family violence and which are described by a purposeful sample of trainee and licensed physicians and social workers in Ontario, Quebec, and Alberta confirmed by a broader population of physician and social work professionals in Canada?
Phase 2 (2021–2022)	((qual)QUAN)	*Qualitative research question:* How do trainee and licensed social workers and physicians in Ontario, Quebec, and Alberta articulate the usability of the VEGA intervention? *Quantitative research question:* What proportion of a sample of trainee and licensed social workers and physicians in Ontario, Quebec, and Alberta report adequate usability (including satisfaction, effectiveness, and efficiency) following the completion of the VEGA intervention? *Mixed method research question:* To what extent do the findings from the “think-aloud” protocols help to understand the usability scores generated from the quantitative strand of data collection?
Phase 3 (2022–2023)	QUAN + QUAL	*Quantitative research question:* Is it acceptable and feasible to implement and evaluate VEGA as a continuing education intervention to improve provider KASB related to recognizing and responding to family violence in Ontario, Alberta, and Quebec primary care settings? *Qualitative research question:* How do providers in primary care and their managers describe the acceptability and feasibility of VEGA as a continuing education intervention to improve their KASB for recognizing and responding to family violence? *Mixed method research question:* How does clinical consultation data, as well as interviews with providers and managers, help to describe the acceptability, feasibility, and perceived impact of implementing and evaluating VEGA as a continuing education intervention in primary care settings within Ontario, Quebec, and Alberta?

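### Phase 2 correlates satisfaction with pre/post KASB scores and names no baseline adjustment, so the result can reflect starting level rather than learning

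*Protocol article*

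**What the plan says.** Under Phase 2, Quantitative and integrated data analysis, the article lists among the displays to be produced "correlations between continuous user satisfaction scores and pre/post-practitioner scores on KASB measures". It names no change score, partial correlation or regression on the pre score.

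The data come from one group measured twice. The Phase 2 Data collection section puts the KASB assessments "immediately prior (time 1; pre-assessment) and immediately following their think-aloud protocol (time 2; post-assessment". The post-assessment alone also asks participants about the clinical environment, "as well as their satisfaction with usability of the VEGA intervention (e.g., System Usability Scale (SUS". Satisfaction is therefore observed once, after exposure, and KASB is observed before and after on the same people.

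The plan is to "recruit a convenience sample of up to 20 trainee (~ 10 social work; 10 physician) and 20 licensed practitioners", so at most about 40 people. That number rests on the detection of usability problems, not on the precision of a correlation. The analysis section opens in descriptive terms: "Quantitative data will be analyzed and interpreted via estimates of central tendency and dispersion".

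**The concern.** Someone reading a correlation between satisfaction and KASB scores in a phase headed as covering usability and education outcomes will naturally take it as a sign of whether people who found VEGA usable also learned more. The named quantities do not isolate that.

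- The pre score is taken before VEGA is seen. Its correlation with satisfaction can describe who is satisfied, but not learning.
- The post score carries the starting level forward. If people who start with more knowledge are also more satisfied, satisfaction and post score will correlate even when satisfaction has nothing to do with what was gained.
- A simple change score does not repair this. For a given post-on-pre relation, change is negatively related to the starting score, so the baseline artefact returns with its sign reversed.

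A link between satisfaction and starting level is plausible here. The sample pools trainees with licensed practitioners and social workers with physicians, groups that may differ in both. The article gives no data on whether they do.

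At stake is the interpretation of one exploratory display. It is, however, the only named analysis that relates satisfaction to KASB scores.

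**Working it through.** The article gives no expected correlation, standard deviation, alpha or power for this analysis, so there is no figure of its own to reproduce. The check concerns what the named correlations would show when there is nothing to find.

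**Inputs**
- n = 40: the planned maximum (20 trainees plus 20 licensed practitioners), Sampling and qualitative data collection.
- r(SUS,pre) from 0.2 to 0.5: assumed.
- r(pre,post) from 0.4 to 0.8: assumed.
- Equal variance of pre and post scores, for the change-score formula: assumed.
- Two-sided 5% level: assumed, and used only as a yardstick, since the article plans no test.

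**Formulae.** Take the case where SUS has zero partial correlation with the post score given the pre score. Then:
- r(SUS,post) = r(SUS,pre) × r(pre,post)
- r(SUS,change) = [r(SUS,post) − r(SUS,pre)] / √(2 − 2·r(pre,post))
- partial r(SUS,post | pre) = 0 by construction

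**Worked example** with 0.4 and 0.6:
- r(SUS,post) = 0.4 × 0.6 = 0.24
- r(SUS,change) = (0.24 − 0.40)/√(2 − 1.2) = −0.16/√0.8 = −0.18

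**Over the assumed range**

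| r(SUS,pre) | r(pre,post) | r(SUS,post) | r(SUS,change) | chance of p<0.05 for r(SUS,post), n = 40 |
|---|---|---|---|---|
| 0 | any | 0 | 0 | 5% |
| 0.2 | 0.4 | 0.08 | −0.11 | 8% |
| 0.2 | 0.8 | 0.16 | −0.06 | 17% |
| 0.4 | 0.6 | 0.24 | −0.18 | 32% |
| 0.5 | 0.4 | 0.20 | −0.27 | 23% |
| 0.5 | 0.8 | 0.40 | −0.16 | 73% |

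The last column uses the Fisher z approximation. For the bottom row, atanh(0.40) × √37 = 0.424 × 6.08 = 2.58, and Φ(2.58 − 1.96) = 0.73. The critical |r| at n = 40 is about 0.31. If r(SUS,pre) were negative, all the signs would reverse.

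**Simulation check** (trivariate normal, n = 40, 20,000 runs, zero partial link). For input pairs (0.3, 0.6), (0.5, 0.6) and (0.5, 0.8), the unadjusted satisfaction–post correlation averaged about 0.18, 0.30 and 0.40 and reached p<0.05 in 20%, 47% and 74% of runs. The partial correlation averaged about 0 and did so in about 5% of runs in all three cases.

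**Precision of the adjusted estimate.** With one covariate, the half-width around zero on the z scale is 1.96/√(40 − 3 − 1) = 1.96/6 = 0.327, and tanh(0.327) = 0.32. The 95% interval is therefore roughly ±0.3.

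**The case against.** The strongest reply is that the article never sets out to estimate a link between usability and gain. The Phase 2 quantitative question in Table 1 asks what proportion of the sample "report adequate usability (including satisfaction, effectiveness, and efficiency) following the completion of the VEGA intervention", and the other two Phase 2 questions concern how users articulate usability and how the think-aloud findings explain the scores. The Phase 2 introduction lists usability and educational impact as two things to describe, not as an association. A reader might infer that connecting the two is the declared purpose of this analysis, or that its result will decide what is changed before Phase 3. The documents support neither: no hypothesis or threshold is attached to it, and usability changes can be decided from problem type, frequency and severity, task completion, time on task and SUS scores. The Discussion also says the non-randomized design rules out causal claims. All of this stands and limits the weight of the point.

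The wording is also ambiguous. A reader might infer that the article commits to unadjusted separate scores. It does not say so, and a fuller document may define the quantity. That stands too, but the article does name the analysis and its variables, and neither natural reading of the phrase removes the starting level.

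The pre-score correlation has descriptive value in its own right. If it is shown beside the post-score correlation, a reader can see any baseline association. That is a partial safeguard, but it does not supply the adjusted estimate.

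Finally, the size is hypothetical, and adjustment is not perfect: measurement error in the pre score can leave some baseline confounding behind. Both are correct.

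**Conclusion.** The point holds in a limited form. As worded, the Phase 2 correlations do not separate an association with learning from an association with starting level, whether the phrase means separate scores or change. When satisfaction has no link with post score given pre score, the satisfaction–post correlation would be about 0.08 to 0.40 and the satisfaction–change correlation about −0.06 to −0.27. These figures rest wholly on assumed correlations and, for change, on equal variances. The artefact is zero if satisfaction is unrelated to the pre score.

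The consequence is minor. It would be too strong to say that the article draws a wrong inference or that a Phase 3 decision is at risk, because the article attaches neither an inference nor a decision rule to this display. What remains is an improvement available at almost no cost to an exploratory analysis.

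**What to change.** Define the quantity in the Phase 2 analysis section:

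- Keep the correlation of SUS with the pre score, described as showing who is satisfied.
- For each KASB measure, add the partial correlation of SUS with post score given pre score, or equivalently the SUS coefficient from a regression of post score on pre score and SUS, with a 95% interval.
- Label these estimates exploratory and non-causal, and note that error in the pre score may leave some residual baseline confounding.

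The cost is a change of wording and one degree of freedom among about 40 participants. No new data are needed, since both scores are already collected on the same people, and the article already uses regression in Phases 1 and 3. The wide interval should be reported as it is, so that an estimate near zero is not read as showing no association.

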### Phase 3: Determining the acceptability and feasibility of implementing and evaluating VEGA in primary care

Continuing to be guided by stage 3 (initial implementation) of the AIF, the primary aim of phase 3 is to determine the acceptability and feasibility of implementing and evaluating VEGA to improve HSSP KASB related to recognizing and responding to family violence in the primary care setting. Our secondary objectives for phase 3 are to determine exploratory estimates of the educational impact for the VEGA intervention, as well as describe the usefulness of implementation strategies to support and sustain VEGA educational impacts in the primary care setting. We will address our objectives using a concurrent mixed method research design; quantitative and qualitative strands of data collection and analysis will occur in parallel and be given equal priority [49]. Quantitative data will provide essential information about HSSP enrollment, retention, attrition, and data completeness; we will also generate exploratory estimates of education effect and variance. The qualitative strand of data collection will provide corroborating information about the acceptability and feasibility of the VEGA intervention in the primary care setting, as well as HSSP perceptions of perceived value and impact of the VEGA intervention and our implementation strategies. Table 3 details the specific acceptability, feasibility, and proof-of-concept objectives for phase 3 mapped to their type of outcome assessment, any relevant hypotheses, and analysis.

**Table 3 Tab3:** Primary and secondary objectives, outcome variables, hypotheses, and analysis for phase 3 of the RISE Project

Objective	Focus	Outcome measure; ***data source***	Criteria for success/hypothesis	Analysis
